#### Implementation outcomes

We will conduct focus groups with participants (as consumers) and healthcare providers in a community advisory board (as setting-level participants) We will use the implementation framework and taxonomy defined by Proctor et al. [38] to guide our evaluation of the relative advantage of Athena over the decision aid alone from the perspective of stakeholders at multiple levels (patients, healthcare systems, system administrators, policy-makers). The taxonomy of implementation outcomes and their applied definition are shown in the Table 1.

**Table 1 Tab1:** Taxonomy of implementation outcomes

		Level of analysis (measurement)		
**Outcome**	**Definition**	**Consumer level**	**Healthcare provider level**	**Setting level**
Acceptability	Stakeholder perception that Athena is acceptable	What needs to change in Athena design and delivery?	What needs to change in Athena design and delivery?	Acceptability of Athena delivery of integrated PrEP/MOUD
Adoption	Intention to employ Athena in practice	Interaction time/frequency and quality	Barriers/facilitators to staff using Athena for WICL in each setting	Barriers/facilitators to using Athena for WICL in each setting
Feasibility	Extent to which Athena can be successfully used in settings serving WICL	Logistical constraints and structural barriers to Athena	Logistical constraints and structural barriers to Athena	Logistical constraints and structural barriers to Athena
Fidelity	Degree to which Athena was implemented as planned	Was Athena delivered as intended?	Was Athena delivered as intended? Athena clinicians will complete pre-session checklists and post-session quality assurance forms	
Implementation cost	Cost of implementing Athena to promote sustainability	Social (stigma), economic cost of participation in Athena	Time, staffing cost of providing Athena	Economic cost of delivering Athena (e.g., reimbursement concerns)
Penetration/Reach	Integration of Athena within settings serving WICL	Recruitment rate; Completion rate; reasons for nonparticipation	Clinician agreement to recommend Athena in settings serving WICL	Administrators’ agreement to employ Athena in settings serving WICL
Sustainability potential	Extent to which Athena becomes institutionalized or is used continuously after study completion in settings serving WICL	What are barriers to Athena continuation after study completion? What would need to change to continue Athena?	What gets in the way of incorporating Athena into current clinical practice and what would need to change?	What are the barriers to scaling up and out Athena beyond the current study? Sustainment measurement system scale

WICL = women in the criminal legal system

MOUD = medications for opioid use disorder

### Data monitoring

A Data Safety Monitoring Board is in place to monitor study progress, and is comprised of experts in criminal legal systems, HIV prevention, and clinical trial methods. A DSMB Charter has been finalized and adopted and is available upon request. DSMB meetings are held a minimum of every 12 months and interim data analyses will occur if and when recommended by the DSMB.

## Statistical analyses

### Sample size

The study is powered on the primary outcome, PrEP initiation. The null hypothesis (H0) is that the proportion of participants initiating PrEP in the Athena arm will be the same as in the decision aid-only arm, whereas the alternative hypothesis (H1) is that the proportion of participants initiating PrEP in the Athena arm will be higher than those in the decision aid-only arm. Based on our clinical trial of a decision aid [33], we anticipate ~ 20% of decision aid-only participants will achieve the primary outcome. Based on our demonstration project of eHealth for PrEP for WICL [36], we anticipate 40–50% of Athena participants will achieve the primary outcome. A total sample size of 212 (106 in each group) would achieve 90% power to detect a 20% absolute difference between the two arms. The proportion in the Athena arm is assumed to be 20% under the null hypothesis and 40% under the alternative hypothesis. The proportion in the decision aid-only arm is < 30%. We will inflate the sample size by 15% to account for attrition and will plan to enroll 250 participants total across 2 sites, which is highly feasible. Though we attempt to minimize missing data by having an objectively measured outcome, we have considered additional plans for missing data that include performing both intention-to-treat and per protocol analyses and performing multiple imputation sensitivity analyses if appropriate.

### Primary analyses

We will evaluate the effect of the Athena strategy, as compared to the decision aid-only (active control) in terms of the primary outcome, PrEP initiation. We will first conduct a descriptive analysis to characterize the study sample in terms of baseline characteristics overall, by treatment arm, and by site. The primary outcome (proportion of participants initiating PrEP) will be compared by treatment arm, site, and race/ethnicity using chi-square techniques. Using an intention-to-treat approach, we will build a multivariate logistic regression model of PrEP initiation; participant characteristics will first be evaluated in univariate models and, if significant at a more liberal p-value threshold, will be used in the multivariate model. In a per-protocol analysis, we will exclude time periods during which individuals are incarcerated during study follow-up, and thus removed from community exposure. The log-rank chi-square test (Kaplan-Meier survival analysis) will be used to compare time to first PrEP visit and time to PrEP initiation between the two arms. We will use descriptive analyses to characterize the PrEP care continuum for the entire sample over 12 months of follow-up, stratified by randomization arm and comprising the following steps [29]: HIV risk, PrEP awareness, completed PrEP visit encounter, PrEP initiation, PrEP adherence, and PrEP care retention by 1-, 3-, and 6-months post-baseline. We will describe engagement in the OUD treatment cascade both overall and by study arm, in terms of treatment initiation, retention, and substance use remission. Participant profiles will be created based on baseline characteristics (within each treatment arm) to assess changes in outcomes over time by site, study arm, and site by study arm. Depending on the distribution of such profiles, we will conduct a latent class analysis to explore characteristics of individuals as they relate to the established profiles. We will assess substance use over time with repeated measures and model using generalized estimating equations (GEE), by study arm and by site. We will assess for the complexity of SUD treatment (e.g., court-mandated vs. voluntary, behavioral vs. MOUD) and explore changes in treatment engagement over time, depending on substance use treatment modality. We will similarly describe diagnosis and treatment engagement for comorbid Hepatitis C and sexually transmitted infections over the 6-month period of observation.

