### Method of Assignment/Randomization

We will use the REDCap automated randomization tool to assign participants into one of two study arms 1:1 and stratified by: (1) site (AL or CT) to balance arms by potentially unmeasured factors that differ by site; (2) past 6-month stimulant use, given high prevalence of stimulant use in this population and association of stimulant use with reduced MOUD retention; [41] and (3) receipt of MOUD at baseline. We selected these strata because we hypothesize these are important effect modifiers and that the implementation strategy will differentially affect these groups. Randomization will be irrespective of baseline decisional preference for PrEP because we expect nearly all will have high interest in PrEP after the decision aid (80–90% based on our pilot clinical trial) [34], but if there are differences in decisional preference between the two groups, we will assess this in the analysis.

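### The primary model picks covariates by a univariate p-value screen with no stated threshold, so the three randomisation strata have no guaranteed place, and the plan does not say whether it or the unadjusted chi-square is primary

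*Protocol article*

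**What the plan says.** The Method of Assignment/Randomization section allocates 1:1 within strata. The first is "site (AL or CT) to balance arms by potentially unmeasured factors that differ by site", the second is "past 6-month stimulant use, given high prevalence of stimulant use in this population", and the third is MOUD receipt at baseline. The reason given is: "We selected these strata because we hypothesize these are important effect modifiers and that the implementation strategy will differentially affect these groups".

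The Primary analyses section gives two analyses of the primary outcome.

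- A simple comparison: "The primary outcome (proportion of participants initiating PrEP) will be compared by treatment arm, site, and race/ethnicity using chi-square techniques". No stratified version is named.
- An intention-to-treat logistic model, with this rule for its covariates: "participant characteristics will first be evaluated in univariate models and, if significant at a more liberal p-value threshold", they enter the final model. The threshold is not given, and nothing exempts the strata from the screen.

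The section does not say which of the two decides the trial. The only cross of a stratum with arm is site by study arm, in the participant-profile work on changes over time.

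**The concern.** Factors important enough to stratify the randomisation belong in the analysis whatever their observed p-values. Here the chi-square ignores them, and the logistic model keeps them only if they happen to pass a screen against the outcome. The same screen lets in characteristics that are associated with the outcome by chance.

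Three things are at stake.

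- The set of covariates, and so the adjusted odds ratio, is settled only after outcomes are seen. Because the odds ratio is non-collapsible, a changing covariate set also changes what is being estimated.
- With two analyses and no stated order, the headline result is open to choice.
- A test that ignores prognostic strata after stratified allocation uses too large a standard error and gives away a little power.

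This is not a gap left by condensing a protocol into an article. The article states the selection rule, and an analysis plan that forced the strata in and dropped the screen would contradict it.

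**Working it through.** **1. The plan's own sample size.** Inputs from the Sample size section: 20% versus 40%, 90% power, 106 per arm, 15% attrition. Two-sided alpha of 0.05 is assumed because none is stated.

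- Unpooled z-test: (1.960 + 1.282)² × (0.16 + 0.24) / 0.20² = 105.1, so 106 per arm. Power at 106 is 90.2%.
- Attrition: 212 / 0.85 = 249.4, so 250.

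Both figures reproduce, and nothing below changes them.

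**2. How often a stratum fails the screen.** Assumed: 250 women, each stratum split 50:50, overall initiation 30% (midway between 20% and 40%), stratum odds ratio 1.65, screen p<0.20.

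- SE of the univariate log odds ratio = √(2 / (125 × 0.21)) = 0.276.
- Expected z = ln(1.65) / 0.276 = 0.501 / 0.276 = 1.81.
- Chance of passing ≈ Φ(1.81 − 1.28) = 0.70. Expected number dropped ≈ 3 × 0.30 = 0.9.
- Simulation, which also allows for the smaller odds ratio when the other strata are left out, gives 1.05 of 3 dropped and all three kept in 27% of trials.
- Other thresholds, same formula: p<0.10 gives Φ(1.81 − 1.645) = 0.57, or 1.3 dropped. p<0.25 gives Φ(1.81 − 1.15) = 0.75, or 0.8 dropped.

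A separate simulation at N = 212, screen p<0.20, varied the stratum effect:

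| Stratum OR (each) | All three strata kept |
|---|---|
| about 1.5 | 9–12% |
| about 2 | 39–51% |
| about 3 | 83–90% |

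**3. Noise covariates admitted.** With 10 irrelevant covariates (assumed), the expected number passing is 10 × 0.20 = 2. At p<0.10 it is 1, and at p<0.25 it is 2.5.

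**4. Size of the chi-square.** Under stratified allocation, the true variance of the arm difference is governed by the mean of p(1 − p) over the eight cells. The chi-square uses p̄(1 − p̄). Take a stratum odds ratio of 2.7 and a common rate of 20%.

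- Cell risks are 4.4% (one cell), 11.0% (three), 25.1% (three) and 47.4% (one). Their mean is 20%.
- Mean p(1 − p) = (0.042 + 3 × 0.098 + 3 × 0.188 + 0.249) / 8 = 0.1436.
- Variance ratio = 0.1436 / 0.16 = 0.897. SD of the test statistic = √0.897 = 0.947.
- Type I error = 2Φ(−1.96 / 0.947) = 3.8%.

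Simulation at odds ratio 2.7, without continuity correction, gives about 3.3 to 4.0%. At odds ratio 2, simulation with N = 212 gives 4.4% for the chi-square against 5.1% for the model that always holds the strata. At 1.65 the chi-square is at about 4.5%. Runs of 1,500 replicates have a Monte Carlo standard error of √(0.05 × 0.95 / 1500) = 0.6 points, so small differences should not be over-read.

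**5. Power, chi-square versus strata always included.**

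- Odds ratio 1.65, N = 250: 93.9% versus 94.2%.
- Odds ratio 2, N = 212: 91.3% versus 91.9%.
- Odds ratio 3, N = 212: 91.6% versus 93.7%.

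**6. Precision of an arm-by-stratum contrast.** For a 50:50 stratum at N = 250 there are 62.5 women per arm per level. SE = √(2 × (0.16 + 0.24) / 62.5) = 0.113, and the 95% half-width is 1.96 × 0.113 = 22 percentage points.

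**The case against.** The strongest reply is that little numerical harm follows. The chi-square errs on the safe side. The screened model keeps type I error near nominal (4.3 to 5.3% in simulation) and shifts the mean log odds ratio by only about 0.01. In any one trial its estimate differs from the strata-adjusted one with an SD of 0.05 to 0.06, against a sampling SD of 0.28 to 0.35. The two harms also do not peak together: where strata are often dropped they matter little, and where they matter most they are rarely dropped. All of this stands, and it limits the point to pre-specification and a small loss of efficiency.

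A reader might go further in four ways that the document does not support.

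- **That the chi-square is severely conservative, near 2.5%.** Values that low appear only with a continuity correction, which the plan does not specify.
- **That the trial cannot answer its effect-modification hypothesis.** All three factors are recorded at randomisation, site by study arm is named, and interaction detail may sit in an analysis plan that is not shown. Its absence from an article is not an error.
- **That "will be compared by treatment arm, site, and race/ethnicity using chi-square techniques" is offered as a test of effect modification.** The article never says so.
- **That decisional preference is subject to a data-dependent adjustment rule.** The text says only that "if there are differences in decisional preference between the two groups, we will assess this in the analysis". It names neither a test of imbalance nor conditional adjustment.

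**Conclusion.** The point holds as a matter of pre-specification. The stated screening rule conflicts with the stratified design: it can drop the design strata, it can admit noise, and no analysis is named as primary.

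The size is moderate for the covariate set (about 1 of 3 strata dropped and 2 of 10 noise covariates admitted at odds ratio 1.65 and p<0.20). It is small for the test: chi-square type I error is about 3.3 to 4.5% over odds ratios of 1.65 to 3, with roughly 0.5 to 2 points of power lost at odds ratios of 2 to 3 and less below that. The main comparison is not invalid, and no inflation of type I error has been shown.

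These figures rest on assumptions that are not in the article: two-sided alpha of 0.05, 50:50 strata, equal stratum odds ratios, a screen at p<0.20 and 10 noise covariates. The finding that the strata are not guaranteed a place needs none of them.

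**What to change.** - Delete the univariate screening step from the primary model.
- Name one intention-to-treat analysis of PrEP initiation as primary, always containing arm, site, past 6-month stimulant use and baseline MOUD. A logistic model with these fixed terms or a stratified test would both serve; the choice of effect measure is the sponsor's.
- List any further baseline covariates in advance, on prior grounds.
- Keep the chi-square as a supporting description.
- Because the strata are described as effect modifiers, arm-by-stratum estimates with confidence intervals can be reported for all three as secondary results, with a note on their low precision.

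The cost is wording in the protocol and analysis plan. The three strata are already collected for randomisation, and the sample size of 212, inflated to 250, does not change.

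### The log-rank comparisons name no strata although randomisation uses three; stratifying them costs almost nothing and recovers some power if the strata predict PrEP initiation

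*Protocol article*

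**What the plan says.** Method of Assignment/Randomization states that the REDCap tool will "assign participants into one of two study arms 1:1 and stratified by" three factors. These are site, "past 6-month stimulant use, given high prevalence of stimulant use in this population and association of stimulant use with reduced MOUD retention", and "receipt of MOUD at baseline". The reason given for the choice is: "We selected these strata because we hypothesize these are important effect modifiers and that the implementation strategy will differentially affect these groups". The Intervention arm section adds that resources will probably differ between the two states and gives this as one reason for stratifying by site.

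Under Primary analyses, the time-to-event sentence reads: "The log-rank chi-square test (Kaplan-Meier survival analysis) will be used to compare time to first PrEP visit and time to PrEP initiation". The comparison is of one arm with the other, and the sentence mentions no strata. The neighbouring sentences do name site where it is meant: "The primary outcome (proportion of participants initiating PrEP) will be compared by treatment arm, site, and race/ethnicity using chi-square techniques", and the repeated-measures model of substance use is by arm and by site. No Cox model or other adjusted time-to-event analysis is described.

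**The concern.** When allocation is balanced within strata that predict the outcome, part of the chance variation between arms is removed by design. An unstratified log-rank test still counts that variation in its variance. It then rejects less often than its nominal level under the null and gives away some power under the alternative. Adjusting the logistic model for initiation (yes/no) does not change this, because the log-rank is a separate test. For time to first PrEP visit it is the only between-arm test that the article states.

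What is at stake is efficiency in two supporting analyses, not the validity of the trial.

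**Working it through.** **The plan's own figure.** Sample size gives 20% vs 40%, 90% power, 212 women (106 per arm), 15% attrition and 250 enrolled. Two-sided alpha of 0.05 is assumed, since the article does not state it. With unpooled variance:

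n per arm = (1.96 + 1.2816)² × (0.2×0.8 + 0.4×0.6) / 0.20² = 10.508 × 0.40 / 0.04 = 105.1, rounded up to 106.

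212 / (1 − 0.15) = 249.4, rounded up to 250. Both figures reproduce. Both rest on the binary endpoint and do not involve the log-rank test.

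**The two tests compared.** At each event i, let a = 1 if the event is in the Athena arm and p = the Athena share of those at risk.
- Unstratified: U = Σ(a − p), V = Σp(1 − p), statistic U²/V.
- Stratified: compute U and V within each stratum k, statistic (ΣU_k)² / ΣV_k.

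Both are referred to 3.84.

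**Simulation.**
- From the article: 250 women, 1:1 allocation, three stratification factors, 6-month follow-up, 20% initiating in the control arm, 40% in the Athena arm, 15% attrition.
- Assumed: binary factors (2×2×2 = 8 strata), equal stratum sizes, permuted blocks of 4, exponential times, dropout at 0.027 per month (1 − exp(−6×0.027) = 15%), and a prognostic hazard ratio (HR) of 1, 1.5, 2 or 3 for each factor. A smaller effect, 20% vs 35%, was also run.
- 6,000 trials per setting. Simulation error is about 0.3 points for type I error and 0.3 to 0.6 points for power.

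| HR per factor | Type I error, unstratified → stratified | Power, 20% vs 40% | Power, 20% vs 35% |
|---|---|---|---|
| 1 | 5.2% → 5.1% | 92.2% → 92.1% | 73.5% → 73.0% |
| 1.5 | 4.3% → 4.6% | 92.9% → 93.1% | 74.3% → 74.9% |
| 2 | 4.0% → 4.8% | 93.5% → 95.0% | 75.2% → 78.3% |
| 3 | 3.2% → 5.0% | 95.3% → 97.7% | 77.3% → 85.2% |

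The change in power from stratifying, at 20% vs 40% and 20% vs 35% respectively, is −0.1 and −0.5 points at HR 1, +0.2 and +0.6 at HR 1.5, +1.5 and +3.1 at HR 2, and +2.4 and +7.9 at HR 3. The last row needs all three factors to be that strong at once.

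**Cross-checks.** A separate simulation of 212 women, with assumed stratum odds ratios of 1.5 to 2.5, gave the same direction:
- type I error 3.9–4.9% unstratified against 4.7–5.4% stratified;
- power at 20% vs 35% of 70.3–70.9% against 71.7–73.1%;
- a gain of about 0.3 to 1 point at 20% vs 40%.

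A third run used 250 women, about 15% dropout and unequal strata with 80% stimulant users. Stratifying cost at most about 0.5 points when the strata were not prognostic, changed little at HR 1.5, and gained about 1.7 points (20% vs 40%) and 3.3 points (20% vs 35%) at HR 2. Unstratified type I error there fell to about 4%.

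**The case against.** The strongest reply is that the article is silent, not wrong. It neither calls the log-rank unstratified nor rules out strata, and the full protocol or SAP may specify them. That stands as a limit on how firmly the point can be put. But the sentence names a two-arm test next to others that do name site, so the text as it reads describes the plain version. A better specification is available from data already collected.

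Second, the strata are described as effect modifiers, not as predictors of initiation, and the reason for stimulant use concerns MOUD retention. A reader might infer that the loss of power is certain; the documents do not support that, because they give no prognostic figure and at HR 1 nothing is lost. Still, if a factor modifies the effect, initiation must differ across its levels in at least one arm. The article itself also expects resources, and in the Discussion insurance coverage, to make PrEP access harder in some settings than in others.

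Third, this is a supporting test. A reader might infer that the trial is underpowered or its error rate unsafe. Neither follows: any error is conservative, the stated power rests on the binary endpoint, and unstratified log-rank power at 20% vs 40% was 92% or more in every setting with 250 enrolled. Handling of the strata matters more in the logistic model, where "participant characteristics will first be evaluated in univariate models and, if significant at a more liberal p-value threshold, will be used in the multivariate model", but that is a separate analysis.

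Fourth, eight strata may be sparse, since stimulant use is said to be common. If 80% are users and the other two factors split evenly (assumed), each non-user stratum has 250 × 0.20 / 4 = 12.5 women. The run with 80% users shows the cost is still at most about half a point. The objection does justify fixing any pooling rule in advance.

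Fifth, one common hazard ratio fits poorly with hypothesised effect modification, and overall Kaplan-Meier curves pair naturally with an unstratified test. Both remarks stand and shape the fix.

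**Conclusion.** The point holds as a minor improvement. Randomisation uses three strata, and the log-rank comparisons as described use none. If the strata predict initiation, the unstratified test is mildly conservative and loses some power: about nil at HR 1 to 1.5 per factor and roughly 1.5 to 3 points at HR 2. If they do not predict it, stratifying costs at most about half a point. The trade therefore favours stratifying.

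The sizes rest on assumed prognostic strengths, two-sided alpha of 0.05, binary factors and exponential times. The direction was the same in all three simulations. The validity of the tests and the stated 90% power for the binary endpoint are not affected.

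**What to change.** State that time to first PrEP visit and time to PrEP initiation are each compared by a log-rank test stratified by site, past 6-month stimulant use and baseline MOUD. Keep the overall Kaplan-Meier curves by arm for display. Fix in advance, blind to arm, any rule for pooling sparse strata, for example a minimum stratum size and the order in which factors are dropped. Report a stratified Cox hazard ratio with its 95% CI, described as an average over strata, alongside the planned site comparisons because effects are hypothesised to differ.

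The cost is a few sentences of analysis text. The stratum values are already recorded at randomisation, and no change to sample size or data collection is needed.

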PrEP adoption gaps are significant for WICL. To access PrEP, women must accurately estimate their own and their partners’ HIV risk and be aware of PrEP, which are major obstacles for WICL and women who use drugs [26–31]. Patient-centered decision aids can align risk perceptions and increase PrEP awareness by merging patient preferences with evidence-based practices. In a prior study, we applied international standardized criteria to develop, test, and report on the first PrEP decision aid [32] and tailored it to women with OUD [33, 34], including trauma-responsive adaptations [35]. We found the decision aid was feasible to administer, acceptable to women and stakeholders, and effective at modifying PrEP preference, but had modest effect on PrEP uptake, in part, because women need to be actively linked to HIV prevention services. We also have successfully enrolled > 100 WICL and their risk network members in an eHealth program for PrEP, demonstrating feasibility, acceptability, and efficacy at increasing PrEP initiation, though the program did not address MOUD [36, 37]. This study builds on our prior work by integrating MOUD and PrEP into an eHealth intervention.

This study responds to the urgent need to reach WICL for life saving, evidence-based HIV PrEP and MOUD by using an innovative healthcare delivery model that integrates services and lowers social and structural barriers to entry. We will reach WICL and evaluate key clinical and implementation outcomes of an integrated PrEP/MOUD delivery model using eHealth and combined with a dedicated PrEP decision aid, as compared to the PrEP decision aid alone with standard of care. We aim to generate sufficient data to drive innovative solutions into the next phase of scaling up and implementing the eHealth delivery model for integrated PrEP/MOUD.

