## Methods

### Study design

This study is a multi-site two parallel-arm unblinded randomized clinical trial comparing the “Athena strategy,” a low-demand model that includes a PrEP decision aid and eHealth delivery of integrated PrEP/MOUD, to a PrEP decision aid-only in terms of patient-level engagement in the PrEP care continuum among WICL with OUD, considering key participating site differences. The primary clinical outcome is PrEP initiation over six months; secondary outcomes are 6-month PrEP retention and engagement in the OUD treatment cascade. We will assess for the complexity of SUD treatment (e.g., court-mandated vs. voluntary; behavioral vs. MOUD) and changes in treatment engagement over time. Exploratory outcomes include diagnosis and treatment of comorbid Hepatitis C and sexually transmitted infections. We will also assess scale-up potential of the Athena strategy in terms of modelled long-term outcomes and how stakeholders interact with eHealth for integrated PrEP/MOUD in WICL in two diverse epidemiological and implementation contexts, using standardized definitions of implementation outcomes [38]. In a state transition model, we will estimate averted HIV infections and quality-adjusted life-year (QALY) gains at individual and population levels over a 10-year time horizon [39]. We will incorporate multi-level perspectives on implementation through focus groups using nominal group technique (NGT), structured surveys, and in-depth interviews.

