### Measures

As shown in the Supplementary Table, the primary outcome of the study is PrEP initiation, which we measure by pharmacy fill date (record review) with a signed release of information. The secondary outcome is PrEP adherence by objective measure, which we assess with a urine assay for tenofovir levels (for participants initiating tenofovir-based PrEP) and injection dates for patients initiating injectable cabotegravir for PrEP. Additional health behavior outcomes of interest are shown in the Table, including self-reported PrEP adherence, 6-month PrEP care retention, use of other HIV prevention tools, engagement in the OUD treatment cascade, and new diagnoses of HIV, viral hepatitis, STIs, or pregnancy. We will review the EHR medication list for PrEP and/or MOUD prescriptions after each clinical visit. If patients receive PrEP and/or MOUD prescriptions outside of our respective EHR-covered health systems, the research assistant will obtain prescription fill and refill dates from clinics and pharmacies with a signed release of information and a phone call on each follow-up interview day.

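### PrEP retention and OUD treatment engagement, named as secondary outcomes, are only described by arm, so no between-arm effect or interval is planned for PrEP retention, MOUD initiation or MOUD retention

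*Protocol article*

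**What the plan says.** The Study design section of the protocol article sets up a two-arm randomised comparison with PrEP initiation as primary outcome, and states that "secondary outcomes are 6-month PrEP retention and engagement in the OUD treatment cascade". The Measures section differs: "The secondary outcome is PrEP adherence by objective measure". It then lists additional outcomes of interest, "including self-reported PrEP adherence, 6-month PrEP care retention, use of other HIV prevention tools, engagement in the OUD treatment cascade" among them.

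The Primary analyses section gives the methods. For PrEP: "We will use descriptive analyses to characterize the PrEP care continuum for the entire sample", stratified by arm, with adherence and care retention as later steps of that continuum. For OUD: "We will describe engagement in the OUD treatment cascade both overall and by study arm", covering starting treatment, staying in it and remission of substance use.

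The same section assigns chi-square tests and logistic regression to PrEP initiation, log-rank tests to time to first PrEP visit and time to PrEP initiation, and a GEE by arm and site to repeated measures of substance use. The Secondary analyses section covers simulation modelling, survey summaries and qualitative work.

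**The concern.** Describing, comparing and modelling are used as different activities within one section. The two outcomes that Study design calls secondary fall under describing. A summary by arm commits the trial to no effect measure and no statement of uncertainty, so a reader would judge a difference by eye.

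This matters more here than for a routine secondary outcome. The Background says the earlier eHealth PrEP programme did not address MOUD and that integrating it is what this study adds; the stated aim is to "evaluate key clinical and implementation outcomes of an integrated PrEP/MOUD delivery model". MOUD is also part of what the Athena arm is offered. Whether Athena changed MOUD initiation or retention is therefore a central question after PrEP initiation.

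Unadjusted percentages would also be hard to read. Eligibility does not depend on baseline MOUD status, so each arm mixes women already on MOUD with women who are not. Baseline MOUD receipt is plausibly a strong predictor of later engagement, and randomisation is already stratified on it.

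**Working it through.** **Outcome by outcome, from the protocol article**

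| Outcome | Status in Study design | Status in Measures | Method in Primary analyses |
|---|---|---|---|
| PrEP initiation | Primary | Primary | Chi-square, logistic regression, log-rank |
| Time to first PrEP visit | Not listed | Not listed | Log-rank |
| PrEP retention, 6 months | Secondary | Additional | Descriptive, by arm |
| Objective PrEP adherence | Not listed | Secondary | Adherence is a step of the descriptive continuum |
| OUD cascade: MOUD initiation, retention | Secondary (as cascade) | Additional (as cascade) | Descriptive, overall and by arm |
| OUD cascade: substance use remission | Secondary (as cascade) | Additional (as cascade) | Descriptive; the GEE of substance use by arm bears on it |

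Whichever section is followed, no between-arm estimate is named for the secondary outcome, apart from what the substance use GEE contributes. Changes in treatment engagement are explored by treatment modality, not by arm. The profile-based analysis is by arm and site but names no outcome.

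**The plan's own sample size.** Inputs from the Sample size section: 20% versus 40%, 90% power, 106 per arm, 15% attrition. Two-sided alpha of 0.05 is my assumption, since the article does not state it. With unpooled variance:

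- n per arm = (1.96 + 1.2816)² × (0.20×0.80 + 0.40×0.60) / 0.20² = 10.51 × 0.40 / 0.04 = 105.1, rounded up to 106, so 212 in total.
- Enrolment = 212 / 0.85 = 249.4, rounded up to 250, or 125 per arm.

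The stated figures reproduce. They concern PrEP initiation only; no precision is stated for the other outcomes.

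**Precision for OUD engagement.** The article gives no rate, so I assume the same rate p in both arms. Half-width = 1.96 × √(2p(1−p)/n).

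- p = 50%, n = 106: 1.96 × √(0.50/106) = 13.5 points.
- p = 50%, n = 125: 1.96 × √(0.50/125) = 12.4 points.
- p from 30% to 60%: 12.3 to 13.5 points at 106 per arm, and 11.4 to 12.4 at 125.

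Near 50%, an observed 10-point gap would have an interval of about −3.5 to 23.5 points (106 per arm) or −2.4 to 22.4 (125 per arm). Over control rates of 30% to 60%, the difference detectable with 80% power is about 18 to 19 points at 106 per arm and 17 to 18 at 125.

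**Precision for PrEP retention.** Among all randomised women, retention cannot exceed initiation, planned at about 20% in control and 40% (up to 50%) in Athena. If half of initiators are retained (an assumption), the rates are 0.5 × 20% = 10% and 0.5 × 40% = 20%. Half-width = 1.96 × √((0.10×0.90 + 0.20×0.80)/n).

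- n = 106: 1.96 × √(0.25/106) = 9.5 points.
- n = 125: 1.96 × √(0.25/125) = 8.8 points.

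Here a 10-point gap has an interval of about 0.5 to 19.5 points, or 1.2 to 18.8, and just excludes zero.

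**The case against.** The strongest reply is that this is a condensed article. Effect measures, intervals and covariates for non-primary outcomes usually sit in the analysis plan, and describing by arm does not forbid an interval. The study is powered only on PrEP initiation, no multiplicity control is described, and Measures ranks retention and OUD engagement as additional outcomes, for which description may be proportionate.

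Part of this stands. The full plan may say more, and a crude difference could be worked out from by-arm counts. But the article is not silent: it states a method for these outcomes, and that method contrasts with those it gives elsewhere in the same section. Nor does Measures rescue the plan, because the outcome it names as secondary sits in the same descriptive continuum. Lack of power argues for an interval rather than against one.

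A reader might infer more than the article supports:

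- That nothing on the OUD side is compared between arms. The GEE of substance use by arm contradicts this, and remission is a step of the cascade. The gap is MOUD initiation and retention.
- That any 10-point difference would be compatible with no effect. This holds for OUD engagement near 50%, but not for PrEP retention at 10% versus 20%.
- That adjusting for baseline MOUD can only narrow the interval. Narrowing is expected but not guaranteed in a finite sample.
- That month-6 data will exist for every randomised woman. The Sample size section allows for 15% attrition, and Follow-up ends participation after a positive HIV or pregnancy test and disenrols women incarcerated for more than six months.

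**Conclusion.** The point holds in limited form. As the article stands, the outcomes that Study design calls secondary receive only descriptive summaries by arm, and no between-arm effect or interval is planned for MOUD initiation, MOUD retention or PrEP retention. The article also contradicts itself on which outcomes are secondary.

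The uncertainty left unshown is about 12 to 14 points either side of an arm difference for OUD engagement, and about 9 to 10 points for PrEP retention. The first rests on an assumed rate near 50%, the second on assumed rates of 10% and 20%, both with 106 to 125 women per arm. The primary analysis and the sample size are unaffected. This is a worthwhile improvement to the reporting of secondary outcomes, not a flaw that threatens the trial.

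**What to change.** 1. Reconcile Study design and Measures so that one list of secondary outcomes applies throughout.
2. For each outcome on that list, replace the descriptive wording with a between-arm risk difference and 95% CI at month 6, by randomised arm, adjusted for the stratification factors: site, past 6-month stimulant use and baseline MOUD receipt. A logistic model standardised to the sample is one suitable way to obtain it.
3. Use the multiple imputation already foreseen in the Sample size section as a sensitivity analysis for women without month-6 data, and state how women whose participation ended early are counted.
4. Label these estimates as not powered, and keep the step-by-step PrEP and OUD cascades as a descriptive display.

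The change is to wording and analysis only. It needs no additional participants, and the stratification factors are recorded at randomisation. The downside is a little more analysis work and some additional unpowered estimates that must be interpreted with caution.
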